#### Dietary adequacy and nutrition related symptoms

Dietary intake and adequacy will be assessed by the study dietitian at T0, T1, and T2 using a structured dietary interview. In addition, for quantitative assessment, participants will complete a validated digital food frequency questionnaire, Foodbook24 [40]. Nutrition related symptoms will also be assessed using the validated Gastrointestinal Symptom Rating Scale (GSRS) [41], and the Simplified Nutritional Appetite Questionnaire (SNAQ) [42].

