### Study design

Using a convergent parallel mixed-methods study design, ReStOre II will be carried out as a randomised controlled trial with two arms: i) an intervention group offered the 12 week ReStOre II programme in addition to usual care, and ii) a control group receiving usual care. The flow of participants through the study is presented in Fig. 1. The study will recruit participants from three large teaching hospitals in Dublin, Ireland (St James’s Hospital, St Vincent’s University Hospital, and Tallaght University Hospital). Ethical approval has been granted from their respective research ethics committees and any subsequent amendments to the trial protocol will be submitted for their approval. The study will be conducted in accordance with the Declaration of Helsinki.

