### Randomisation and blinding

Following successful completion of baseline assessments, including a CPET, participants will be formally registered on the trial and will be randomised to the ReStOre II programme or the usual care control group. Block randomisation will be performed using a computer-generated randomisation list. Randomisation will be administered independently by the CRF at SJH. Study assessments will be performed by an assessor concealed to allocation. Given the design of the ReStOre II programme, it will not be feasible to blind either the research staff responsible for delivering the ReStOre intervention or trial participants to their allocation.

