#### Dietary counselling

One-to-one dietetic sessions will be delivered during week 1, week 2 and fortnightly thereafter, or more frequently if required. Dietetic sessions will be delivered by a registered dietitian. Weight and circumferential measures will be recorded at each session and dietary intake will be assessed using tailored dietary interview strategies (incorporating 24-h recalls and qualitative information such as meal pattern and eating strategies). Nutritional requirements will be estimated using validated equations combined with appropriate stress and activity factors. The education delivered in the dietetic sessions will be individualised to participants’ needs, considering any dietary challenges such as dysphagia or malabsorption. The target for participants is to optimise dietary intake, ensuring adequate energy and micronutrient status, in alignment with the World Cancer Research Fund (WCRF) [31] and European Society for Clinical Nutrition and Metabolism (ESPEN) [32] guidelines for cancer survivors .

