### Safety

Patient safety will be paramount to the implementation of the ReStOre II trial. Standard safety measures will include; written medical clearance, and successful completion of a medically supervised CPET prior to trial commencement. All trial assessments and supervised exercise sessions will take place in the CRF which is located within the confines of SJH and is covered by their emergency response team. All adverse events will be documented, and serious adverse events will be communicated to the SJH/TUH and SVUH research ethics committees. Weight loss is a particular concern for UGI cancer survivors, and accordingly the study dietitian will monitor weight closely during the ReStOre II programme.

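### The T1 and T2 dietary interview is assigned to a dietitian who very likely knows allocation, although the protocol says without exception that assessors are concealed

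*Protocol article*

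**What the plan says.** Randomisation and blinding makes two statements. The first covers all outcome assessment and names no exception: "Study assessments will be performed by an assessor concealed to allocation". The second names those who cannot be blinded: "it will not be feasible to blind either the research staff responsible for delivering the ReStOre intervention or trial participants to their allocation".

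Dietary adequacy and nutrition related symptoms names the person who assesses one of the outcomes: "Dietary intake and adequacy will be assessed by the study dietitian at T0, T1, and T2 using a structured dietary interview". Table 3 lists this interview among the secondary outcomes at those three visits. Foodbook24, which participants complete themselves, is the second instrument for dietary intake.

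Safety uses the same job title for a task during the intervention: "the study dietitian will monitor weight closely during the ReStOre II programme".

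Dietary counselling describes who runs the one-to-one sessions in more general terms: "Dietetic sessions will be delivered by a registered dietitian". It adds: "Weight and circumferential measures will be recorded at each session".

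**The concern.** The blinding statement is unqualified, so a reader will take every study assessment after randomisation as made by someone who does not know the arm. For the dietary interview, the article's own staffing points the other way: the named interviewer also follows participants through a programme that one arm receives.

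Dietary quality and nutritional status are the subject of a stated secondary aim. An interview about intake and adequacy depends on how questions are put and followed up. An interviewer who knows the arm can influence what is elicited and recorded, without meaning to. If the results are reported under the general blinding statement, readers would give this comparison more protection against bias than it has.

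**Working it through.** No figure in the document bears on this point, so the check sets the statements side by side.

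1. **Is the interview covered by the blinding statement?** Yes. Table 3 lists it as a secondary outcome instrument at T0, T1 and T2, and the blinding statement makes no exception for any outcome.

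2. **Who does it?** The section on dietary adequacy names the study dietitian, for all three visits.

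3. **What else does that role do?** Safety has the study dietitian watch weight during the ReStOre II programme. Both sections use the identical title with the definite article, so the natural reading is one role.

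4. **Who is in the programme?** Study design describes "an intervention group offered the 12 week ReStOre II programme in addition to usual care". The control arm has usual care only, as the section on the standard care group repeats. Anyone monitoring participants during the programme therefore sees intervention participants and no controls.

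5. **Does that reveal allocation?** The document does not say so, but the step is short. Close monitoring of weight during a programme given to one arm identifies the members of that arm, and participants not seen there are controls.

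6. **Which visits are affected?** Randomisation comes after baseline: "Following successful completion of baseline assessments, including a CPET, participants will be formally registered on the trial and will be randomised". At T0 there is no allocation to know. The conflict is confined to T1 and T2, two of the interview's three visits.

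7. **Is the interviewer also the counsellor?** Probably, but this is not shown. Weight is recorded at the one-to-one dietetic sessions, of which Table 1 schedules seven (weeks 1, 2, 4, 6, 8, 10 and 12). That makes those sessions the likely setting for the monitoring described under Safety. However, the section on dietary counselling speaks only of a registered dietitian and does not use the study dietitian's title. Steps 1 to 6 do not depend on this link.

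8. **How much of the trial is touched?** One of the two dietary-intake instruments in Table 3. The primary outcome is measured by CPET and is not affected.

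**The case against.** The strongest reply is that the interviewer's knowledge of allocation is inferred. The article nowhere equates the registered dietitian who counsels with the study dietitian who interviews. A condensed article may leave out that two dietitians are employed, one of them concealed, and the general blinding statement could then be the rule under which the interview is to be read. Part of this stands. A reader might infer that the person who gave the counselling also assesses its result, and the document does not establish that. The reply does not remove the conflict, because the interview and the weight monitoring are given to the same title and no second dietitian is mentioned. This is a stated property contradicted by another statement, which is different from a detail left out.

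A second reply is that the interview is described as structured and no grading method is given. That stands too: a reader might infer a subjective score, but the text does not describe one. Elicitation by an interviewer is enough for the concern.

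A third reply is that the outcome is secondary and its aim is worded as exploration. This is correct. It limits the importance of the point, and there is no confirmatory status to lose.

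Finally, Foodbook24 is no clean substitute. Participants know their allocation, and those who have been counselled on diet may report more favourably on a questionnaire as well. This stands, and the fix has to say so.

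**Conclusion.** The concern holds in limited form. As written, the statement of concealed assessment is contradicted for the dietary interview at T1 and T2, because the named interviewer very likely knows allocation. This rests on two assumptions: that the title study dietitian means one role in both sections, and that monitoring participants during a one-arm programme reveals the arm.

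The likely consequence is interviewer bias in favour of the intervention. A reader might take that direction as certain, but nothing in the document proves it, and the size of any bias cannot be computed from it. T0 and the CPET outcome are unaffected. The point deserves correction because it concerns the accuracy of a blinding claim, but it does not threaten the trial's main conclusion.

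**What to change.** Reconcile the sections on randomisation and blinding, dietary adequacy, and safety in one of two ways.

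- **Keep the claim.** State that the T1 and T2 dietary interviews are done by existing staff who have no part in the programme and are concealed from allocation. This costs one sentence if such staff are available. If they are not, use the second option.
- **Qualify the claim.** Amend the blinding statement to list the dietary interview as an exception, report it as unblinded, and use Foodbook24 for the between-arm dietary comparison. The article already assigns Foodbook24 the quantitative role and schedules it in both arms at T0, T1 and T2, so only wording changes. Add that this removes interviewer bias but leaves self-report bias, because participants are not blinded.

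The price of the second option is that the interview data carry less weight in the comparison between arms.

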#### Quality of life

HRQOL will be determined by the European Organisation for Research and Treatment of Cancer Quality of Life Questionnaire (EORTC-QLQ-C30 version 3.0) and its relevant subscales. The EORTC-QLQ-C30 consists of functional scales (physical, role, cognitive, emotional, and social), symptom scales (fatigue, pain, nausuea and vomiting), global health status and HR-QOL scale, in addition to several single item symptom measures [43]. Cancer specific QOL issues will be assessed using the appropriate cancer subscale; QLQ-OG25 (oesophago-gastric cancer), QLQ-HCC18 (hepatocellular cancer), and QLQ-PAN26 (pancreatic cancer). To interpret the core questionnaire and cancer specific subscales, higher functional scores indicate greater functioning, whereas lower symptom scores indicate less symptom burden.

#### Fatigue

Fatigue will be measured using the Multidimensional Fatigue Inventory (MFI-20). The MFI-20 is a 20-item scale that measures the impact of fatigue in five dimensions: general, physical, cognitive, motivation and usual activities. It is scored from 0 to 20, with a cut-off score of ≥13 indicating severe fatigue. The psychometric properties of the MFI-20 have been tested and determined strong validity and reliability [44].

#### Qualitative data collection

Qualitative methods will be utilised to investigate intervention participants’ perceptions of the impact of the ReStOre II programme on their daily lives. Data will be collected through semi-structured focus group discussions immediately post-intervention (T1) and individual interviews at 3-months follow-up (T2). Focus groups at T1 will specifically explore the impact of the ReStOre II programme on mental, physical, and social well-being, whilst also examining the value of the group-based exercise programme and education talks to recovery. Individual interviews at T2 will focus more on examining the maintenance of health behaviours acquired during participation in the ReStOre programme. Interviews and focus groups will be led by a researcher experienced in qualitative methods and audio-recorded followed by verbatim transcription in preparation for data analysis.

#### Cost analysis

Programme implementation costs will be analysed in consideration of programme costs (e.g. clinician salaries, overheads and equipment costs). Changes in HR-QOL scores will be analysed and cost-effectiveness ratios calculated. The patterns of service use and related costs will be assessed for patients in each arm of the study, and alongside the costs of the intervention a comparison will be made of the total costs and outcomes, to estimated cost-effectiveness ratios.

#### Biosample collection

Serum, plasma, and whole blood samples will be collected at T0, T1, and T2 for the purpose of establishing a national UGI cancer survivorship biobank. Samples will be processed and stored at -80 °C at the Trinity Translational Medicine Institute, St James’s Hospital, Dublin 8 for future analyses to explore the mechanistic pathways underpinning the impact of multidisciplinary rehabilitation in survivorship.

#### Intervention Fidelity

In line with recent findings by Nilsen et al. [45], our research group also recognises the need to enhance reporting of adherence in exercise oncology trials. To this end, whilst also reporting on traditional adherence variables in our current research portfolio, we are now also endeavouring to report on additional variables adapted from drug trials in all our exercise oncology trials [45]. The ReStOre II trial will report on standard variables including supervised session attendance and the completion rate of home-based exercise sessions. Akin to our current PRE-HIIT trial examining high intensity interval training in advance of major thoracic surgery for cancer of the lung or oesophagus [46], ReStOre II will also include a number of novel adherence variables which are outlined fully in Table 4.

**Table 4 Tab4:** Exercise adherence variables

Variable	Definition
Total number of supervised sessions attended	Total number of supervised sessions attended in the CRF at SJH
Total number of homebased sessions completed	Total number of homebased sessions reported in exercise diary as complete
Total number of compliant aerobic sessions completed	Total number of aerobic sessions (supervised/unsupervised) where prescribed aerobic exercise dosage was achieved
Total number of compliant resistance sessions	Total number of resistance sessions (supervised/unsupervised) where prescribed resistance training dosage was achieved
Permanent treatment discontinuation	Permanent discontinuation of the ReStOre II programme before week 12
Treatment interruption	Missing at least three consecutive supervised ReStOre II sessions
Dose modification	Number of supervised sessions requiring exercise dose modification
Early session termination	Number of supervised sessions requiring early session termination
Pre-treatment intensity modification	Number of supervised sessions requiring modification because of a pre-exercise screening indication.

### Safety

Patient safety will be paramount to the implementation of the ReStOre II trial. Standard safety measures will include; written medical clearance, and successful completion of a medically supervised CPET prior to trial commencement. All trial assessments and supervised exercise sessions will take place in the CRF which is located within the confines of SJH and is covered by their emergency response team. All adverse events will be documented, and serious adverse events will be communicated to the SJH/TUH and SVUH research ethics committees. Weight loss is a particular concern for UGI cancer survivors, and accordingly the study dietitian will monitor weight closely during the ReStOre II programme.

### Sample size calculation

Using data from the ReStOre pilot RCT [22] and supporting published literature [47], a sample size of 96 (48 per arm) is needed to detect a mean increase of 3.5 ml/min/kg in the intervention arm, assuming a 1.75 ml/kg/min increase in the control arm and standard deviation of change of 2.59 ml/kg/min for each arm, with 90% power at the 5% significance level based on a two-sample t-test. Given an expected attrition rate of 20%, a sample of 120 participants (60 per arm) will be recruited.

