#### Exercise

The exercise component will consist of a 12-week supervised and home-based intervention. The exercise prescription will include both aerobic and resistance training and will be prescribed by a physiotherapist. Supervised group exercise sessions will be held twice weekly during the first 4 weeks to reintroduce exercise to participants in a safe and structured manner. As the programme progresses the frequency of supervised sessions will decrease, and the frequency of home-based exercise sessions will increase. This structure aims to encourage self-management in survivorship and increase autonomy with exercise prescription.

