### Data management and analysis

The Data Management Plan will outline how research data will be handled during and after the project. Outcome assessments will be recorded in a paper-based case report form and then entered into a password protected computer data repository. Data validation will be used to avoid erroneous data entry. All participants will be allocated a unique study code. The key to the study code will be stored securely and separately. All paper records will be stored in locked filing cabinets, in a locked office in a restricted access building with swipe access. Electronic records will be stored on password protected encrypted devices. Upon completion of the trial an anonymised data set will be deposited on a secure online repository in line with open access publication requirements.

Quantitative data analysis will be completed using IBM SPSS software. Baseline characteristics will be presented for each study arm. Values for normally distributed continuous variables will be presented as means (standard deviations), whereas data which does not follow a normal distribution will be presented as median (range). Categorical variables will be displayed as counts and proportions. A linear mixed model will be used to model the longitudinal change in the primary response between the groups, allowing pair-wise deletion for missing data and allowing for within subject correlations in the repeated measures across time. The variance-covariance structure will be decided based on parsimony, and the ReStOre pilot RCT data. The model will inherently adjust for the baseline response variable. The primary endpoint will be the *p*-value for the interaction of time-point with treatment arm. The primary analysis set will comprise an Intention-to-treat group, including all patients with analysable data irrespective of fidelity, compliance, or arm cross-over. Statisticians will finalise a detailed Statistical Analysis Plan prior to the final T3 visit taking place and will remain blinded to study arm until the analysis is complete.

A qualitative descriptive approach [48] will be taken to the analysis of qualitative data. Braun and Clarke’s 6 stage approach to thematic analysis will be used to analyse all data collected [49]. A team of researchers will analyse all transcripts following an agreed process using nVivo 12 (QSR International, Australia).

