### Public and patient involvement (PPI)

ReStOre II will involve a number of PPI initiatives. Firstly, a previous ReStOre participant is a collaborator on the trial and will sit on the TSC, and will review the study protocol, study procedures and documentation. Second, we have incorporated a PPI focused study within a trial (SWAT) into this study [50–53]. The SWAT will explore the effects of patient co-designed participant information on study recruitment rates. The protocol for the SWAT has been published separately [54]. Third, past ReStOre participants will attend the first class of each programme to meet and encourage new participants. Finally, a patient representative will be invited to speak at the education symposium.

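### Group classes run in the intervention arm only, but the sample size assumes independent participants; if change in VO2peak correlates within class, the planned standard error is too small and the 90% power optimistic

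*Protocol article*

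**What the plan says.** **Delivery.** The Exercise section states: "Supervised group exercise sessions will be held twice weekly during the first 4 weeks". Table 1 also lists group education sessions. The section on public and patient involvement shows that the programme is run repeatedly, in classes: "past ReStOre participants will attend the first class of each programme". The Standard care group section describes no group contact for controls.

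**Sample size.** The Sample size calculation gives 96 evaluable participants (48 per arm), "needed to detect a mean increase of 3.5 ml/min/kg in the intervention arm", "assuming a 1.75 ml/kg/min increase in the control arm", with a "standard deviation of change of 2.59 ml/kg/min for each arm, with 90% power at the 5% significance level based on a two-sample t-test". With 20% attrition this becomes 120 randomised. No design effect is mentioned.

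**Analysis.** Under Data management and analysis, the primary outcome is analysed with a linear mixed model "allowing for within subject correlations in the repeated measures across time". No other source of correlation is named. The covariance structure is left to parsimony and the pilot data, and a detailed statistical analysis plan is to be finalised before the last T3 visit.

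**The concern.** Randomisation is by individual, but intervention participants are then placed in classes and controls are not. This is a partially nested design. Classmates share sessions, education talks and visits from past participants. If some classes do better than others for such reasons, the outcomes of classmates are correlated. The mean of the intervention arm then varies more than an independent-samples formula allows.

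Three things are at stake if that correlation is positive. The confidence interval for the primary comparison is too narrow. The unadjusted test can reject too often under a null of no average effect. A valid analysis of 48 per arm has less power than stated. A within-subject covariance structure does not address this, because it concerns repeated measures on one person and not different people in one class.

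**Working it through.** **Inputs from the protocol:** difference 3.5 − 1.75 = 1.75 ml/kg/min; SD of change 2.59 in each arm; 48 evaluable per arm; 5% level, taken as two-sided; 20% attrition.

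**Assumptions (not in the protocol):** m = 6 to 10 evaluable participants per class and ICC = 0.01 to 0.05. The check uses change scores, as the sample size calculation does, not the full repeated-measures model.

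**Step 1: the stated figure.** The two-sample t-test needs 47.01 per arm, hence 48. Power at 48 is 0.906 (0.912 by normal approximation), and 96/0.8 = 120. The plan's arithmetic is correct under independence, with no spare allowance beyond rounding up.

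**Step 2: variance with classes in one arm.** Let DE = 1 + (m − 1) × ICC. The variance of the difference is (2.59²/48) × (1 + DE), against (2.59²/48) × 2 under independence. The ratio of correct to planned SE is √[(1 + DE)/2]. For m = 6 and ICC 0.05, DE = 1.25 and the ratio is √(2.25/2) = 1.061.

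**Step 3: consequences.**
- Type I error of the unadjusted test = 2 × [1 − Φ(1.96/ratio)].
- Power from the variance effect alone = Φ(1.75/SE − 1.96).
- Power of a class-adjusted analysis uses a noncentral t with Satterthwaite df = (v1 + v0)² / [v1²/(48/m − 1) + v0²/47], where v1 = 2.59² × DE/48 and v0 = 2.59²/48.

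| m | ICC | SE ratio | Type I error, unadjusted | Power, variance effect only | Power, Satterthwaite df |
|---|---|---|---|---|---|
| 6 | 0 | 1.000 | 0.050 | 0.912 | 0.888 |
| 6 | 0.01 | 1.012 | 0.053 | 0.905 | 0.880 |
| 6 | 0.05 | 1.061 | 0.065 | 0.877 | 0.845 |
| 8 | 0 | 1.000 | 0.050 | 0.912 | 0.879 |
| 8 | 0.01 | 1.017 | 0.054 | 0.902 | 0.866 |
| 8 | 0.05 | 1.084 | 0.071 | 0.863 | 0.812 |
| 10 | 0 | 1.000 | 0.050 | 0.912 | 0.868 |
| 10 | 0.01 | 1.022 | 0.055 | 0.899 | 0.849 |
| 10 | 0.05 | 1.107 | 0.077 | 0.849 | 0.773 |

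The ICC 0 rows show the cost of having few classes (48/6 = 8 down to 48/10 = 4.8), which is incurred even if there is no clustering.

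**Step 4: enrolled or evaluable class size.** If 6 to 10 is the number enrolled, 20% attrition leaves 4.8 to 8. From m = 4.8, ICC 0.01 to m = 8, ICC 0.05, the SE is 1% to 8% larger, the type I error 5.2% to 7.1%, and Satterthwaite power 0.89 to 0.81.

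**Step 5: simulation of the unadjusted t-test** (40,000 runs). For m = 6, ICC 0.05, the type I error is 0.063 and the rejection rate at the design effect 0.892. For m = 8, ICC 0.05, the figures are 0.072 and 0.888. If clustering is ignored, the excess of false positives is therefore a larger problem than the fall in the rejection rate.

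**The case against.** The strongest objection is that the size of the ICC is unknown and may be small. Aerobic intensity and resistance loads are individualised, dietetic sessions are one-to-one, and Table 1 sums to 36 home sessions against 13 supervised ones. All supervised sessions are at one facility, and VO2peak is measured individually by an assessor unaware of allocation. This stands as an argument for a modest ICC, but it does not establish zero.

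Second, much of the Satterthwaite loss at low ICC is a degrees-of-freedom penalty of the adjusted model. That also stands: at m = 6, ICC 0.01, power is 0.880, but it is already 0.888 at ICC 0. For this reason both power columns are shown.

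Third, individual randomisation limits the type I argument. If the programme affects nobody, sharing a class creates no correlation. Inflation needs class effects that exist but average to zero.

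Fourth, the protocol leaves the model's detail to a later analysis plan that may add a class term and is not excluded from doing so. The absence of that term here is therefore not in itself an error. The sample size, however, is already fixed on independence.

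A reader might also infer that the protocol regards the group format as an active ingredient, since the focus groups are planned as "examining the value of the group-based exercise programme and education talks to recovery". That is an open qualitative question about recovery, not a statement that grouping drives VO2peak. Nor does the protocol say that instructors differ between classes.

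**Conclusion.** The point holds in conditional form. Classes exist in one arm only, and the sample size makes no allowance for them. Any positive class-level correlation makes the planned SE too small and the 90% optimistic. Under the assumed class sizes and ICCs, the effect ranges from negligible (6 per class, ICC 0.01: SE 1% larger, type I error 5.3%) to material (10 per class, ICC 0.05: SE 11% larger, type I error 7.7%, power 0.85 from variance alone and 0.77 with Satterthwaite df). If those class sizes are enrolment figures, the upper end is milder.

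It would go too far to say that the trial does not have 90% power or that its type I error exceeds 5%. The protocol gives no class size, number of classes or ICC, so neither statement can be derived from it. The figures 96 and 120 are correct on their stated basis.

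**What to change.** 1. Record the programme cohort (class) of every intervention participant from the start. Class cannot be modelled if it was not captured.
2. Fit the primary mixed model with a class random effect in the intervention arm only, controls entering as singletons, with small-sample degrees of freedom (Satterthwaite or Kenward-Roger). At minimum, pre-specify this as a sensitivity analysis of the primary result.
3. Restate the 90% power as assuming no class-level correlation, name the planned class size (enrolled and evaluable), and show power over a stated ICC range. The sample size need not change.

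The cost in data and programming is one variable and one model term. The cost in inference is a wider confidence interval and fewer degrees of freedom, because the class variance would rest on roughly 5 to 8 classes at the assumed sizes, and a less favourable stated power. The class variable also reveals the arm, and the statisticians are to stay blinded until the analysis is complete, so the model must be programmed before they receive it.
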